### Analyses:

#### Probabilistically sample observed episodes as “prevented” by vaccine and re-calculate incidence

We will start with a vaccine for *Shigella* with dosing at 6 and 9 months of age. We will assume 60% efficacy 14-days after administration of the second dose. For simplicity, we will assume 0% efficacy prior to this time point. The Monte Carlo simulation will then be performed over the dataset with 50,000 samples under two scenarios: vaccine and no vaccine. For the vaccine scenario, we will probabilistically assign whether diarrheal episodes attributable to *Shigella* (defined by AFe > 0.5) would have been prevented assuming 60% efficacy. It is important to note that *Shigella* infections increase with age therefore, 60% efficacy will not directly translate to a 60% reduction in diarrheal illnesses. Additionally, there is low natural immunity (~20%) against subsequent *Shigella* diarrhea when considering all serotypes and species, so prior infection will not be factored in (Rogawski McQuade 2020 J Infect Dis),

at least initially. In a later iteration of the analyses, we may incorporate potential clustering of prevented episodes within children (i.e. all episodes among 60% of children are prevented, rather than 60% of episodes prevented overall, regardless of the child). We may also incorporate the potential for herd immunity among children too young to be vaccinated, partial efficacy after a single vaccine dose, different vaccine schedules (6&9, 9&12, 12&15 months), effects on severity in addition to or instead of incidence, and varying levels of vaccine efficacy. For the no vaccine scenario, no *Shigella*-attributable episodes would be prevented. We will conduct a sensitivity analysis where we define shigella diarrhea by any detection of shigella rather than AFe > 0.5.

We will estimate the expected reductions due to a *Shigella* vaccine in the following metrics:

1. Antibiotic treated severe *Shigella* diarrhea episodes

$$\left( \frac{N_{\text{antibiotic treated severe diarrhea episodes attributed to Shigella}} * \frac{\text{total number of diarrhea associated courses}}{\text{Total number of linked diarrhea associated courses}}}{\text{total child years of follow up}} \right) * 100$$

2. Antibiotic treated *Shigella* diarrhea episodes

$$\left( \frac{N_{\text{antibiotic treated diarrhea episodes attributed to Shigella}} * \frac{\text{total number of diarrhea associated courses}}{\text{Total number of linked diarrhea associated courses}}}{\text{total child years of follow up}} \right) * 100$$

3. Antibiotic treated severe diarrhea episodes of any etiology

$$\left( \frac{N_{\text{reported severe antibiotic treated diarrhea episodes}} * \frac{\text{total number of diarrhea associated courses}}{\text{Total number of linked diarrhea associated courses}}}{\text{total child years of follow up}} \right) * 100$$

4. Antibiotic treated diarrhea episodes of any etiology

$$\left( \frac{N_{\text{reported antibiotic treated diarrhea episodes}} * \frac{\text{total number of diarrhea associated courses}}{\text{Total number of linked diarrhea associated courses}}}{\text{total child years of follow up}} \right) * 100$$

5. Antibiotic courses overall

$$\left( \frac{N_{\text{reported antibiotic courses}} * \frac{\text{total number of diarrhea associated courses}}{\text{Total number of linked diarrhea associated courses}}}{\text{total child years of follow up}} \right) * 100$$

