### Summary:

This analysis is the third step (Aim 2) in a larger project to estimate the impact of enteric vaccines on etiology-specific diarrhea, antibiotic use, and exposure of subclinical infections to antibiotics among children in low-resource settings. Specifically, this analysis will estimate the impact of introducing two-dose series enteric vaccines with varying vaccine schedules (6&9, 9&12, 12&15 months), levels of indirect protection, effects on severity but not incidence, and vaccine efficacies. We will begin the analyses by focusing on hypothetical *Shigella* vaccines, with plans to analyze vaccines against additional enteric pathogens (e.g. *Campylobacter*, norovirus, enterotoxigenic *Escherichia coli* (ETEC), and rotavirus (vaccine available)). As in the previous analyses, we will analyze existing data from 1,715 children from the Malnutrition and Enteric Disease (MAL-ED) study.

Based on the different scenarios outlined above, will extend the results from Aim 1a (attributing diarrheal episodes that cause treatment) and from Aim 1b (attributing bystander antibiotic exposures for subclinical pathogens to diarrheal pathogens). Analyses will be performed at the level of diarrheal episode (N=6,677) from Aim 1a. We will then merge in the number of subclinical pathogen exposures to antibiotics per diarrheal episode from Aim 1b. We will use the attributable fractions per episode (AFe) for diarrheal pathogens that were calculated in Aim 1a where a pathogen with an AFe >0.5 is considered the cause of the diarrheal illness. We will then simulate how much antibiotic exposure calculated in Aims 1a (<https://osf.io/e4bqr/>) and 1b (<https://osf.io/3asxh/>) can be prevented with a vaccine. To simulate, we will perform Monte Carlo simulations with random sampling of the dataset with replacement to a sample size of 50,000. 95% confidence intervals for all parameters will be estimated by bootstrap with 1,000 resamples.

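### The prevention rule has no coverage or timeliness term, so the simulated reductions are the direct effect at 100% on-time two-dose coverage, not the impact of introducing the vaccine

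*Protocol*

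**What the plan says.** The Summary sets the target: "this analysis will estimate the impact of introducing two-dose series enteric vaccines", for young children in low-resource settings. The scenario factors it names are schedule, indirect protection, effect on severity, and efficacy.

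The Analyses subsection on sampling prevented episodes fixes the base case:

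- Schedule: "We will start with a vaccine for *Shigella* with dosing at 6 and 9 months of age".
- Efficacy: "We will assume 60% efficacy 14-days after administration of the second dose".
- Before that: "For simplicity, we will assume 0% efficacy prior to this time point".
- Rule: a random draw decides whether each *Shigella*-attributed episode "would have been prevented assuming 60% efficacy".

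The unit is the episode: "Analyses will be performed at the level of diarrheal episode (N=6,677) from Aim 1a". Possible later variations are clustering of prevented episodes within children, herd immunity for children too young to be vaccinated, one-dose efficacy, other schedules, severity effects and other efficacy levels. The protocol mentions neither coverage nor the spread of ages at which doses are received.

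**The concern.** The effect of introducing a vaccine depends on how many children complete the series and when. The simulation rule depends on neither. The vaccine is hypothetical and the data already exist, so the date of the second dose can only be the scheduled age, and every child is treated as having received it.

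The protocol declares other simplifications openly, such as zero early efficacy and the omission of natural immunity. It does not declare full, on-time coverage. A reader of the reported rates averted per 100 child-years and percent reductions would take them as the result of introduction, without knowing that they are conditional on complete and punctual uptake.

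**Working it through.** The protocol states no impact figure, so there is none to reproduce. The check has two parts: what coverage the rule implies, and how the result moves when coverage changes.

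**Inputs.** Efficacy VE = 0.60, from 14 days after a second dose at 9 months (protocol, Analyses). Assumed, because the protocol gives no value: two-dose coverage c, and the share s of *Shigella* episodes that fall in the protected window.

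**Step 1: coverage implied by the rule.** The expected direct reduction is c × VE × s. A 50,000-draw simulation of the protocol's rule gave reductions of 60.1%, 54.3%, 48.1% and 41.7% at s = 1.0, 0.9, 0.8 and 0.7. VE × s is 60%, 54%, 48% and 42%. The rule is the case c = 1.

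**Step 2: effect of coverage.** The full-coverage figure divided by the figure at coverage c is (VE × s)/(c × VE × s) = 1/c, whatever s is.

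| c (assumed) | c × 0.60 | Reduction at s = 1.0 | Reduction at s = 0.8 | Excess, 1/c − 1 |
|---|---|---|---|---|
| 100% | 0.60 | 60% | 48.0% | 0 |
| 90% | 0.54 | 54% | 43.2% | 11% |
| 80% | 0.48 | 48% | 38.4% | 25% |
| 70% | 0.42 | 42% | 33.6% | 43% |

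The same factor applies to the absolute differences and percent changes for metrics 1–7, if their linkage correction factors are held fixed.

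**Step 3: late second dose.** Assume follow-up to 24 months. Protection starts at 9 + 14/30.4375 = 9.46 months.

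- Incidence proportional to age: s = 1 − (9.46/24)² = 0.845 and the reduction is 50.7%. A one-month delay gives 48.6%.
- Flat incidence: the reduction is 36.4%, and 33.9% with a one-month delay.

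The delay costs about 2 to 2.5 percentage points. For comparison, 80% coverage in the first case gives 0.8 × 50.7% = 40.5%, a loss of about 10 points.

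**Step 4: mean age of *Shigella* diarrhea (the secondary outcome).** Same assumptions, incidence proportional to age. Let k = 1 − 0.60c be the fraction of episodes left after protection starts. Mean age = [9.46³/3 + k(24³ − 9.46³)/3] / [9.46²/2 + k(24² − 9.46²)/2].

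- No vaccine (k = 1): 4608/288 = 16.0 months.
- c = 1 (k = 0.40): 2012.5/142.0 = 14.2, a shift of −1.8 months.
- c = 0.8 (k = 0.52): 2531.6/171.2 = 14.8, a shift of −1.2 months.

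Multiplying the full-coverage shift by 0.8 would give about −1.5, so this outcome cannot be rescaled by hand.

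**Step 5: what could offset the excess.** Let indirect protection h act on all *Shigella* episodes not directly prevented. The h that restores the full-coverage direct figure is 1 − (1 − VE·s)/(1 − c·VE·s). At c = 0.8 this is 1 − 0.40/0.52 = 23% for s = 1.0, and 1 − 0.58/0.664 = 13% for s = 0.7.

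**The case against.** The strongest reply is that this is a staged model of a hypothetical vaccine. The Summary also describes the aim as the amount of antibiotic exposure a vaccine could prevent, and full coverage is a normal reference case for that. This stands as a defence of running the case. It is no defence of leaving the condition unstated when the result is described as the impact of introduction.

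A second reply is that varied efficacy already does the work: 80% coverage with 60% efficacy has the same expected result as 48% efficacy. For uptake unrelated to risk this is arithmetically true, for mean age as well. But the protocol never presents varied efficacy as standing for uptake, and an efficacy value cannot represent late doses or missed doses concentrated in higher-risk children. The clustering variant does not fill the gap either, since it only moves the 60% from episodes to children.

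Scenario values could be left to an analysis plan that is not shown. However, the protocol itself fixes the prevention rule and lists the factors to be varied, and coverage is not among them.

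Stronger readings are tempting, and the document does not support them:

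- **The plan overstates impact on balance, or gives an upper limit.** The base case also leaves out indirect protection and one-dose efficacy, both of which would raise the impact. Step 5 shows that modest indirect protection could cancel the excess.
- **The one-dose option is empty.** It is not: it can act in every simulated child between the first dose and the start of full protection.
- **A comparison with stewardship would favor the vaccine.** That comparison is only a possibility under future directions, and no uptake is defined for stewardship.

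**Conclusion.** The point holds for the direct effect. As written, the rule yields the direct reduction at 100% on-time two-dose coverage, while the Summary calls the result the impact of introduction. For any real coverage c below 100%, the direct reduction is too large by a factor of 1/c: 11%, 25% or 43% at assumed c of 90%, 80% or 70%. This assumes that missing the series is unrelated to *Shigella* risk and that children without a second dose get no protection, in line with the protocol's zero early efficacy. The coverage values are assumptions, not figures from the protocol. The net bias, once indirect and one-dose effects are counted, cannot be determined from the document. Timeliness matters much less than coverage. The change is worth making because it costs little and brings the output closer to the stated question.

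**What to change.** 1. State in the Analyses section that the base case assumes every child receives both doses at the scheduled ages. Label its results as the direct effect under full, on-time two-dose coverage.
2. Add two-dose coverage to the varied factors, for example 70%, 80%, 90% and 100%. Apply it as a vaccinated/unvaccinated draw per child identifier before the episode-level efficacy draw, so that all episodes of one child share one status. Renew the draw in each bootstrap resample.
3. Report metrics 1–7 and the mean age of *Shigella* diarrhea at each coverage level.
4. A scenario with a delayed second dose is optional, given its small effect.

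The cost is one extra draw per child and more scenarios to report. The simulation resamples episodes, so the child identifier must be carried through. No new data are needed. The direct-effect figures below 100% coverage will look less favorable.

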## 6. Antibiotic exposures to subclinical pathogens due to treatment of *Shigella*

$$\left( \frac{N \text{ times any bacterial pathogen exposed to abx during diarrhea caused by } Shigella * \frac{\text{total number of diarrhea associated courses}}{\text{Total number of linked diarrhea associated courses}}}{\text{Total number of linked courses}} \right) * \left( \frac{\text{Total number of courses}}{\text{Total child years of follow up}} \right) * 100$$

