## 7. Antibiotic exposures to subclinical pathogens overall

$$\left( \frac{N \text{ times any bacterial pathogen exposed to antibiotic} * \frac{\text{total number of diarrhea associated courses}}{\text{Total number of linked diarrhea associated courses}}}{\text{Total number of linked courses}} \right) * \left( \frac{\text{Total number of courses}}{\text{Total child years of follow up}} \right) * 100$$

To estimate the expected reductions in #1-7 listed above, we will compare the relative and absolute differences between the vaccine and no vaccine simulations.

Relative difference, is expressed as a ratio of the metric between the vaccine simulations and the no vaccine simulation, which will be calculated as:

$$\frac{\text{vaccine simulation}}{\text{no vaccine simulation}}$$

Or the percent change as:

$$\frac{\text{vaccine simulation} - \text{no vaccine simulation}}{\text{no vaccine simulation}}$$

Absolute difference, which captures the true distance between two values, will be calculated as:

$$| \text{vaccine simulation} - \text{no vaccine simulation} |$$

As a secondary outcome, we will estimate the average age of *Shigella* diarrhea under the vaccine and no vaccine scenarios to determine whether the vaccine would be expected to increase the average age of disease.

Future directions:

Once we have the *Shigella* vaccine simulation running, we will compare the impact of a *Shigella* vaccine to that for other enteric vaccines, most importantly rotavirus. We may also include a comparison to a broad stewardship intervention that is not targeted to a specific pathogen.

Added Sept 12, 2022:

We will estimate the expected reductions in diarrheal episodes caused by *Shigella* and any etiology (regardless of whether the episode was treated):

1. Severe *Shigella* diarrhea episodes

$$\left( \frac{N_{\text{severe diarrhea episodes attributed to Shigella}} * \frac{\text{total number of diarrhea episodes}}{\text{Total number of diarrhea episodes validly tested by TAC}}}{\text{total child years of follow up}} \right) * 100$$

2. *Shigella* diarrhea episodes

$$\left( \frac{N_{\text{diarrhea episodes attributed to Shigella}} * \frac{\text{total number of diarrhea episodes}}{\text{Total number of diarrhea episodes validly tested by TAC}}}{\text{total child years of follow up}} \right) * 100$$

3. Severe diarrhea episodes of any etiology

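### The numerators of metrics 6 and 7 count any bacterial pathogen, contradicting their titles and the Summary, which concern subclinical (bystander) pathogens; read literally, they include the treated cause

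*Protocol*

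**What the plan says.** Metric 6 is titled "Antibiotic exposures to subclinical pathogens due to treatment of" Shigella. Its numerator is the number of "times any bacterial pathogen exposed to abx during diarrhea caused by" Shigella. Metric 7 is titled "Antibiotic exposures to subclinical pathogens overall", and its numerator is the number of "times any bacterial pathogen exposed to antibiotic". Both numerators are restricted to bacteria. Neither is restricted to subclinical pathogens.

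The Summary gives the data source: "We will then merge in the number of subclinical pathogen exposures to antibiotics per diarrheal episode from Aim 1b". It describes Aim 1b as "attributing bystander antibiotic exposures for subclinical pathogens to diarrheal pathogens". It also sets the causal rule: "a pathogen with an AF e >0.5 is considered the cause of the diarrheal illness".

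The Analyses section adds: "We will conduct a sensitivity analysis where we define shigella diarrhea by any detection of shigella rather than AFe > 0.5". It does not say what happens to the merged subclinical count under that definition. Relative and absolute differences between the vaccine and no-vaccine simulations are planned for all seven metrics.

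**The concern.** A pathogen that meets the causal rule is not subclinical in that episode. Shigella is a bacterium and is present in every episode attributed to it, so a count of any exposed bacterium takes in the organism being treated. The title and the formula then measure different things.

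Metrics 6 and 7 are the only ones of the seven that measure the bystander benefit of a vaccine, which is one of the project's stated targets. If the target organism is counted, direct and bystander exposure are mixed. The Protocol's future directions also include a comparison with rotavirus. Rotavirus is not a bacterium, so on the literal formula a Shigella vaccine would be credited with preventing self-exposures and a rotavirus vaccine would not.

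**Working it through.** The Protocol gives no result or expected value for either metric, so there is no stated figure to reproduce. The check compares the literal count with a bystander-only count.

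**Inputs**
- From the Protocol: vaccine efficacy VE = 0.60 from 14 days after the second dose; cause defined by AFe > 0.5.
- Assumed, because the Protocol does not give them: b, the mean number of bystander bacteria per treated episode (0.5, 1, 2), taken as equal for all courses; f = 0.8, the share of Shigella episodes after full efficacy; s, the share of courses given for Shigella; c, the share given for any bacterial cause, Shigella included; one causal bacterium per such episode.

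The share of Shigella episodes prevented is VE × f = 0.60 × 0.8 = 0.48. The scaling terms in the formulas are the same for both counts and cancel in the comparisons below.

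**Metric 6, absolute.** Averted per 100 treated Shigella episodes:
- bystander only: 100 × 0.48 × b
- literal: 100 × 0.48 × (b + 1)
- inflation: (b + 1)/b = 3.0, 2.0 and 1.5 for b = 0.5, 1 and 2

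At b = 1 this is 48 against 96. A simulation of 200,000 episodes gave 48.2 and 96.3.

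**Metric 6, relative.** If b is the same in preventable and other episodes, the ratio of vaccine to no vaccine is 1 − 0.48 = 0.52 on either count. The simulation gave 0.519 for both. The two would differ only as far as the bystander count differs between episodes before and after full efficacy.

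**Metric 7, absolute.** Only Shigella episodes are prevented, so the inflation is again (b + 1)/b.

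**Metric 7, relative**
- bystander only: 0.48 × s
- literal: 0.48 × s × (b + 1)/(b + c)

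| s, c | bystander only | literal, b = 0.5 | b = 1 | b = 2 |
|---|---|---|---|---|
| 10%, 20% | 4.8% | 10.3% | 8.0% | 6.5% |
| 5%, 15% | 2.4% | 5.5% | 4.2% | 3.35% |

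For example, at s = 10%, c = 20% and b = 1: 0.48 × 0.10 × 2/1.2 = 8.0%. The factor (b + 1)/(b + c) exceeds 1 whenever c < 1. With equal b, the direction therefore does not depend on the shares chosen.

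**If the Aim 1b count is the numerator and excludes the cause.** The literal and bystander-only counts coincide, and the inflation in the main analysis is zero.

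**Any-detection sensitivity analysis.** Let r be the share of treated any-detection Shigella episodes in which Shigella has AFe ≤ 0.5, and let b now count bacteria other than Shigella. If Aim 1b classed that Shigella as subclinical, the merged count averages b + r where b is wanted. The absolute inflation in metric 6 is (b + r)/b, between 1 and (b + 1)/b. The Protocol does not give r.

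**The case against.** The strongest reply is that the Summary already fixes the source. It says a subclinical count will be merged in, it describes Aim 1b as being about bystander exposures, and both metric titles agree. The phrase about any bacterial pathogen may simply mean pooled over bacterial species within that count. This stands. A reader might infer that Shigella is in fact counted as its own bystander and that the exposures averted will be overstated. The Protocol does not establish that. Whether the Aim 1b count leaves out the cause is settled in a linked plan that is not at hand.

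Three things remain:
- Nothing in the two formulas refers back to Aim 1b. They state one restriction and omit the one in their titles, so an analyst who follows them would count Shigella.
- The merge is per diarrheal episode. Metric 7 is an overall figure divided by all linked courses, so the merge sentence does not clearly define its numerator.
- The shorthand reading does not settle the any-detection analysis. It could be said that the recode is programming detail, and that Aim 1b may not have classed low-AFe Shigella as subclinical. Both are fair, and they limit this part to one sensitivity analysis and to a possibility.

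The rotavirus comparison is a future direction with no metrics specified, so its distortion is also conditional on the literal reading.

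**Conclusion.** The contradiction between the numerators and their titles and stated source is on the page and should be corrected. A bias in the main results is possible but not shown.

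On the literal reading, the absolute reductions in metrics 6 and 7 are inflated by (b + 1)/b. The relative reduction in metric 7 is inflated too, for instance from 4.8% to between 6.5% and 10.3%. On the Aim 1b reading with the cause excluded, all of this is zero. It would be wrong to infer that the percent change in metric 6 is overstated: it is essentially the same on either reading. Every magnitude rests on assumed values of b, s and c and on about 80% of Shigella episodes falling after full efficacy.

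Under the any-detection definition, Shigella with AFe ≤ 0.5 becomes the cause and may stay in the merged bystander count, even if the main analysis is sound.

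**What to change.** Define both numerators as the number of times a subclinical bacterial pathogen, other than the pathogen or pathogens to which the episode is attributed, is exposed to antibiotics, and name the Aim 1b count as the source. For metric 7, also state where the count for courses outside diarrheal episodes comes from. In the any-detection sensitivity analysis, recompute the count per episode so that Shigella is removed wherever it is reclassified as the cause.

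The cost is two formula edits and a small recode, with no new data. The figures for metrics 6 and 7 may become smaller. If the code already excludes the cause, the main results do not change and the written formulas will match it.
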